## Abstract

**Background:**

The placement of prophylactic intra-abdominal drains has been common practice in abdominal operations including pancreatic surgery. The PANDRA trial showed that the omission of drains following pancreatic head resection was non-inferior to intra-abdominal drainage in terms of postoperative reinterventions and superior in terms of clinically relevant pancreatic fistula rate and fistula-associated complications. The aim of the present PANDRA II trial is to evaluate the clinical outcome with versus without prophylactic drain placement after distal pancreatectomy.

**Methods:**

The PANDRA II trial is a mono-center, randomized controlled, non-inferiority trial with two parallel study groups. In the control group at least one passive intra-abdominal drain is placed at the pancreatic resection margin. In the experimental group no drains are placed. The primary endpoint of this trial will be the Comprehensive Complication Index (CCI) measuring all postoperative complications within 90 days. Secondary endpoints are in-hospital mortality and morbidity, including the rates of postoperative pancreatic fistula, chyle leak, postpancreatectomy hemorrhage, delayed gastric emptying, reinterventions and reoperations, surgical site infection, and abdominal fascia dehiscence. Moreover, length of hospital stay, duration of intensive care unit stay, and the rate of readmission after discharge from hospital (up to day 90 after surgery) are assessed. We will need to analyze 252 patients to test the hypothesis that no drainage is non-inferior to drain placement in terms of the CCI (δ 7.5 points) in a one-sided *t* test with a one-sided level of significance of 2.5% and a power of 80%.

**Discussion:**

The results of the PANDRA II trial will help to evaluate the effect of an omission of prophylactic intraperitoneal drainage on the rate of complications after open or minimally invasive distal pancreatectomy.

**Trial registration:**

German Clinical Trials Register (DRKS), DRKS00013763. Registered on 6 March 2018.

**Electronic supplementary material:**

The online version of this article (10.1186/s13063-019-3442-0) contains supplementary material, which is available to authorized users.

## Background

The placement of prophylactic intra-abdominal drains to reduce postoperative surgical complications has been common practice in abdominal surgery for decades. Recent studies, however, have failed to show any benefit of routine drainage following many abdominal resections including hepatobiliary [1, 2], gastric [3, 4], and colorectal surgery [5, 6]. These studies have shown that surgery can be performed safely without prophylactic drainage. Although the use of prophylactic drains was shown to be unnecessary in other resections, many surgeons fear that abandoning prophylactic drainage after a pancreatic resection could be detrimental due to the high rate and severe consequences of pancreatic fistula. While mortality after pancreatic resections has been significantly reduced, postoperative morbidity following pancreatic surgery remains a concern and is as high as 40–50% even in specialized centers [7–9]. For many surgeons the rationale for inserting drains following pancreatic surgery is to evacuate the blood, bile, pancreatic juice, or chyle that may accumulate after pancreatic surgery, which can serve as an early warning sign of postoperative pancreatic fistula and its associated complications such as postpancreatic hemorrhage. However, the majority of patients do not develop postoperative pancreatic fistula, and experiences with drains in other operations [1–6] suggest that unnecessary drains can cause complications. Drains might serve as a port of entry for bacteria and turn non-infected postoperative fluid collections into abscesses and infected fistula. In addition, drains might cause tissue trauma from suction, erode anastomoses, and cause intestinal leaks [10]. Several randomized and non-randomized trials have attempted to identify risk constellations where placement of abdominal drains after pancreatic surgery seems to be justified [7, 10–13]. Other studies have tried to explore the effectiveness of early versus late removal of abdominal drains [14, 15]. In 2017, the PANDRA trial showed that the omission of drains following pancreatic head resection was non-inferior to intra-abdominal drainage in terms of postoperative reinterventions and superior in terms of clinically relevant pancreatic fistula rate and fistula-associated complications [16]. Therefore, some surgeons have abandoned the routine use of drains in pancreatic surgery. Nonetheless, most pancreatic surgeons continue to use a prophylactic drain. Up to now it is unclear whether routine abdominal drainage after distal pancreatectomy has any effect on the reduction of postoperative complications. The aim of the present PANDRA II trial is to evaluate the clinical outcome of prophylactic drain placement versus no drainage after open or minimally invasive distal pancreatectomy with respect to postoperative complications.

## Study design

### Objectives and hypotheses

The PANDRA II trial investigates differences in the postoperative course after distal pancreatectomy comparing the surgical technique with placement of an abdominal drain versus no placement of an abdominal drain after open or minimally invasive distal pancreatectomy.

The following hypotheses will be tested:H0: The risk of developing postoperative complications is different between the two groups.H1: The risk of developing postoperative complications is equal in both groups.

### Study registration, ethics, and consent

Before inclusion of the first patient, the trial protocol was approved by the ethics committee of the University of Heidelberg (Ethikkommission Medizinische Fakultät Heidelberg, S-675/2017) and the trial was registered (DRKS00013763; UTN: U1111-1207-3031). The trial will be conducted at the Clinical Trial Center (KSC) of the Department of General, Visceral and Transplantation Surgery, University Hospital Heidelberg in the context of Good Clinical Practice and in accordance with the Declaration of Helsinki. Randomization and data management are performed by the KSC. The statistical analysis will be performed independently by the Institute of Medical Biometry and Informatics (IMBI) of the University of Heidelberg. The PANDRA II trial is designed as a mono-center, randomized controlled, non-inferiority trial with two parallel study groups. All patient-related information is subject to medical confidentiality and to medical secrecy according to the European General Data Protection Regulation (DSGVO — Datenschutzgrundverordnung), the Federal Data Protection Act (Bundesdatenschutzgesetz), and the State Data Protection Act (Landesdatenschutzgesetz). Third parties will not have any insight into original data.

### Study population

All patients assigned for distal pancreatectomy at the Department of General, Visceral and Transplantation Surgery, University of Heidelberg, will be screened for eligibility before the operation. Eligible for participation are all patients planned for open or minimally invasive distal pancreatectomy for pancreatic disease. Patients must be at least 18 years of age and provide written informed consent. Patients have to be able to understand character and individual consequences of the clinical trial. The following exclusion criteria have been defined: (1) indication for pancreatic resection with a pancreaticojejunal anastomosis, (2) American Society of Anesthesiologists (ASA) physical status classification ≥4, (3) impaired mental state or language barriers impeding informed consent, (4) participation in another interventional trial with interference of intervention and outcome of this trial (Table 1). During this preoperative visit, patients will be informed about the clinical problem of postoperative complications, the timeline of the PANDRA II trial, and the possible risks and benefits of participation before they will be asked to give their written informed consent.

**Table 1 Tab1:** Eligibility criteria

Inclusion criteria	Exclusion criteria
• Surgical indication for open or minimally invasive distal pancreatectomy • Aged 18 years and over • Ability of subject to understand character and individual consequences of the clinical trial • Informed consent provided	• The subject has a surgical indication for pancreatic resection with a pancreaticojejunal anastomosis • American Society of Anesthesiologists (ASA) physical status classification ≥ IV • Impaired mental state or language problems of the subject • Participation in another interventional trial with interference of intervention and outcome of this trial

### Outcome parameters

Overall postoperative morbidity assessed with the Comprehensive Complication Index (CCI) [17] was chosen as primary endpoint since this parameter considers the patient’s perspective as well as parameters of surgical effectiveness. A score of 0 indicates no complications, whereas 100 is equivalent to death. The index is based on the established Clavien-Dindo classification [18]. The score is validated for the pancreatic surgical population, and a difference of 10 is regarded as a clinically relevant difference [17]. An endpoint reflecting the entire spectrum of complications like the CCI is highly appropriate to compare two different surgical strategies for the abdominal cavity. The score will be calculated respecting all complications within 3 months after the index operation.

Secondary endpoints are in-hospital mortality and also postoperative morbidity up to day 90 after the index surgery, including frequency of postoperative pancreatic fistula according to the definition of the International Study Group of Pancreatic Surgery (ISGPS) 2017 [19]; lymphatic fistula according to the definition of the ISGPS 2017 [20]; postoperative bleeding according to the definition of the ISGPS 2007 [21]; reinterventions and reoperations including computed tomography (CT)-guided placement of drains due to intra-abdominal fluid collection, intra-abdominal bleeding, and/or pancreatic and lymphatic fistula; delayed gastric emptying according to the 2007 ISGPS definition [22]; surgical site infection according to Centers for Disease Control and Prevention (CDC) definition; and abdominal fascia dehiscence. Moreover, operation time and length of hospital stay, duration of ICU stay, as well as the rate of readmission after discharge from hospital (up to day 90 after surgery) are assessed.

### Randomization

All participating patients are randomized intraoperatively once the surgical decision to perform a distal pancreatectomy has been made by the attending surgeon. The randomization will be performed prior to pancreatic resection. Block randomization with varying block sizes is performed with a 1:1 allocation ratio. A computer generated random list was created. The allocation is performed by opening sequentially numbered opaque envelopes containing a card marked “Drainage” or “No Drainage”. The randomization process and assignment of the patients to the respective trial intervention are performed by staff members of the KSC at the University Hospital Heidelberg. If the surgical procedure of a distal pancreatectomy is not accomplished after randomization, e.g., due to inoperability or the need for total pancreatectomy, the patient is excluded from final analysis.

### Standardized surgical approach

#### For both groups

Open or minimally invasive distal pancreatectomy is performed by the surgeon according to local practice. Conversion from laparoscopic to open resection will be documented in the case report form, but does not lead to exclusion of a patient. Additional partial resection of larger veins or arteries (e.g., the superior mesenteric/portal vein or celiac trunk) is allowed. Furthermore, patients with additional resection of other organs (e.g., colon, liver, spleen) or even distal pancreatectomy combined with multivisceral resection are also eligible. The decision to perform an additional splenectomy or cholecystectomy is at the surgeon’s discretion. The type of abdominal incision (longitudinal or transverse laparotomy) as well as the placement of trocars in terms of laparoscopic pancreatic resections is determined by the surgeon performing the procedure. After exploration of the abdominal cavity, the pancreas is revealed and transected by scalpel or by stapler as no differences in pancreatic fistula rate have been reported between different transection techniques. A coverage procedure with, e.g., the falciform ligament or suturing the ventral and dorsal surfaces of the gland by single stitches or running suture of the pancreatic remnant is at the discretion of the surgeon performing the procedure and will be documented. Further manipulation of the pancreatic remnant such as the use of fibrin glue or reinforcement with meshes is not allowed, as these methods have failed to show any benefit [23]. The use of somatostatin and its analogs is not standardized in the trial protocol, but it needs to be documented and will be analyzed separately for both groups.

#### Control group

In the control group at least one drain (open-circuit silicone drain or closed-circuit silicone drain) is placed at the pancreatic remnant for percutaneous drainage just before abdominal wall closure. Amylase values are measured on the third postoperative day in the drained fluid. There is no restriction on the number of days the drains should remain. They can be removed whenever they are no longer needed, justified by the clinical state of the patient.

#### Experimental group

In the experimental group no drains are placed.

### Postoperative data collection and blinding

Postoperative data collection is performed at prespecified time points. Regular visits with study patients on all wards will be performed by clinical investigators and study nurses from the clinical study center in order to collect information on the primary and secondary outcome parameters and to identify any postoperative complication. Two postoperative study visits (3rd postoperative day and 10th postoperative day/ day of discharge) and two follow-up telephone interviews after discharge (30 days and 90 days postoperatively) will be performed (Fig. 1). All surgeons must describe the technique they performed on the pancreas on a standardized form that is sent to them by email on the day of the index operation to record whether patients were treated according to the study protocol and were assigned to their groups truly at random. Blinding to the treatment allocation for participants, research assistants, operating surgeons, data collectors, and outcome assessors is difficult — if not impossible — as drain placement is obvious. However, the primary and secondary outcome measures are objective endpoints that are not influenced by blinding. Therefore, only data analysts will be blinded in this trial.

**Fig. 1 Fig1:**
[figure not shown]
Enrollment, interventions, and assessment schedule of the PANDRA II trial: course of examinations (modified SPIRIT figure)

### Safety aspects

All postoperative complications are monitored during hospital stay and follow-up examinations (up to day 90). Major complications are defined as complications graded IV and V according to the Clavien-Dindo classification [18]. (The Clavien-Dindo classification grades are listed in Additional file 2). The coordinating investigator must be informed about these complications. Additionally, there are evaluations of mortality after including 30 and 90 patients, respectively, into the study. If there is a significantly increased rate of mortality in one of the groups, there will be an early termination of the trial.

### Sample size calculation

The sample size calculation is based on the primary outcome parameter CCI [17] in a non-inferiority design. Assumptions are made on in-house calculations of the CCI on data from the DISPACT trial [24] and the NURIMAS Pancreas study [25] (mean CCI 30; standard deviation 20). A decrease of the CCI by 10 points is considered relevant by patients and clinicians. Therefore, a margin of 7.5 CCI points will be tolerated as non-inferior. With a significance level of 2.5% and 80% power, we need to analyze 113 patients in each group (Nquery 7.0). With an additional dropout of 10%, 126 patients need to be allocated to the no drain and drain arms, respectively. Based on the department’s data, recruitment will be completed within 36 months after inclusion of the first patient.

### Statistical analysis

Non-inferiority of no drain versus drain after distal pancreatectomy will be assessed using a one-sided *t* test. The one-sided significance level is set to 2.5%. The hypotheses to be assessed in the primary efficacy analysis are as follows: H0: μNo Drainage – μDrainage ≥ δ and H1: μNo Drainage – μDrainage < δ, where δ = 7.5 represents the chosen non-inferiority margin and μNo Drainage, μDrainage denote the mean CCI in the no drain and drain groups, respectively. The primary efficacy analysis will be based on the intention-to-treat set according to the intention-to-treat principle. Additionally, an evaluation of the primary outcome will be performed in the per protocol set and in the as treated set (where all patients will be analyzed as they were treated) as sensitivity analyses. Missing data for the primary outcome variable will be replaced by using multiple imputation [26], which takes the covariate treatment group into account by application of the fully conditional specification method. All secondary outcomes will be evaluated descriptively, and descriptive *p* values will be reported together with 95% confidence intervals for the corresponding effects. All analyses will be done using program R 3.2 or higher. Statistical analysis will be performed after closure of the database.

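### The unadjusted primary t test is valid and adequately powered as planned, but a pre-specified adjustment for baseline facts known before randomisation could add precision at almost no cost

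*Protocol article*

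**What the plan says.** Under Statistical analysis, the protocol article states: "Non-inferiority of no drain versus drain after distal pancreatectomy will be assessed using a one-sided" *t* test. It adds "The one-sided significance level is set to 2.5" per cent. The hypotheses concern the difference in mean CCI, no drain minus drain, against a margin of 7.5. No baseline covariate is named for this test. The only covariate named anywhere in that section is treatment group, in the imputation model.

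The Sample size calculation section uses the same unadjusted comparison: "mean CCI 30; standard deviation 20", "Therefore, a margin of 7.5 CCI points will be tolerated as non-inferior", and "With a significance level of 2.5% and 80% power, we need to analyze 113 patients in each group (Nquery 7.0").

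Three other sections bear on what is known before allocation:

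- **Study population:** age of at least 18 is an inclusion criterion, and "American Society of Anesthesiologists (ASA) physical status classification ≥4" is an exclusion criterion. Patients are screened as planned for open or minimally invasive surgery.
- **Randomization:** allocation takes place during the operation, before resection. The scheme is given as "Block randomization with varying block sizes is performed with a 1:1 allocation ratio", with no stratification factor named.
- **For both groups** (Standardized surgical approach): "Conversion from laparoscopic to open resection will be documented in the case report form".

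**The concern.** The population is deliberately broad: ASA I to III, open and minimally invasive surgery, with additional vascular and multivisceral resections allowed. If some of the spread in CCI follows patient or operative characteristics fixed before randomisation, a two-group *t* test leaves that variance in the standard error. A linear model with those characteristics as covariates would remove it.

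Precision matters here. The design has 80% power only if the true difference is zero, and power is lower if omitting the drain is slightly worse. The conclusion depends on whether a confidence limit falls below one fixed number, 7.5. For an outcome compared by its mean, linear adjustment leaves the target of estimation (the difference in mean CCI) and the margin as they are. The question is whether the article passes up precision that it could have at little or no cost.

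**Working it through.** **Inputs from the protocol article:** SD 20, margin 7.5, one-sided level 2.5%, 113 analysed per arm, 10% dropout.

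**Assumptions not in the article:** a true difference of 0, and the share of CCI variance explained by the covariates (R²), shown as a range.

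**Step 1. Reproduce the plan's figure.**

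- Standard error of the difference: 20 × √(2/113) = 2.66 points.
- Noncentrality: 7.5 / 2.66 = 2.82, with 2 × 113 − 2 = 224 degrees of freedom.
- Power from the noncentral *t* distribution: 80.1%. With 112 per arm it is 79.8%, so 113 is the smallest sufficient number.
- Dropout: 113 / 0.9 = 125.6, rounded up to 126 per arm, 252 in total.

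The stated sample size reproduces, so the planned test delivers its stated power without adjustment.

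**Step 2. What is known before randomisation.** Age and ASA class must be established to apply the eligibility criteria. The planned approach is part of the screening description, and conversion can only be documented against an intended approach. Because randomisation is intraoperative, all three precede it. The article does not say that the intended approach is held as a baseline data field, so that one is an inference.

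**Step 3. Power with adjustment.** Three covariate terms (age, ASA I–II versus III, approach) leave 226 − 2 − 3 = 221 degrees of freedom. The residual SD is 20 × √(1 − R²). The half-width of the two-sided 95% interval is t(0.975; 221) × residual SD × √(2/113).

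| Assumed R² | Residual SD | Power at 113 per arm | Half-width (CCI points) | n per arm for 80% power |
|---|---|---|---|---|
| 0% | 20.00 | 80.1% | 5.24 | 113 |
| 2% | 19.80 | 80.9% | 5.19 | 111 |
| 5% | 19.49 | 82.1% | 5.11 | 108 |
| 10% | 18.97 | 84.1% | 4.97 | 102 |

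The first row is the cost if the covariates prove useless. Three degrees of freedom are spent, and power is unchanged at the precision shown. At R² of 10% the gain is 84.1 − 80.1 = 4.0 percentage points, and the half-width shrinks by 5.24 − 4.97 = 0.27 points.

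**The case against.** The strongest reply is that nothing in the plan is wrong. With 1:1 block randomisation and no stratification factor named, the two-group *t* test is a valid comparison of means. It matches the stated hypotheses and the sample size calculation. This stands in full.

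A reader might infer that precision is certainly being lost, because the population is mixed. The article does not support that. No section says that age, ASA class or approach predicts the CCI, and none gives an R², a correlation or a residual SD. A mixed population does not show that outcomes differ between its parts, and excluding ASA IV and above narrows the range of that variable. The gain is therefore unknown, and modest over the lower part of the assumed range (0.8 points of power at 2%, 2.0 points at 5%).

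A reader might also see chance imbalance in approach or ASA class as a second, separate weakness. It is not. Under randomisation such imbalance is not bias, and the standard error of the unadjusted test already allows for it. Any worked example would need an invented share of open operations and an invented CCI difference between approaches. It would also only restate the precision argument.

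Finally, it is not certain that every covariate is recorded in usable form. Age and ASA class appear only as eligibility checks, and the figure with the assessment schedule is not shown. Recording of both is very likely; recording of the intended approach is plausible but inferred.

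What the reply does not remove is the asymmetry. The downside of adjusting is negligible and the upside may be real, so the recommendation does not depend on knowing R². Nor is this a detail left to an unseen analysis plan, because the article itself fixes the unadjusted test as primary.

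**Conclusion.** The point holds as an efficiency recommendation and no more. The planned test is sound and meets its stated power, given SD 20, margin 7.5, 113 per arm and an assumed true difference of zero. It may forgo some precision by not using age, ASA class and probably the intended approach. On an assumed R² of 0% to 10%, the possible gain is 0 to 4.0 percentage points of power, or up to 0.27 CCI points off the half-width of the interval. The article supports neither a known loss nor a claim that the primary analysis is invalid or biased.

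**What to change.** Before database closure and unblinding, pre-specify the following.

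1. **Primary analysis:** a linear model of the CCI on treatment group, age and ASA class (I–II versus III), with robust standard errors because the CCI is bounded and may be skewed. Add the intended surgical approach if it was recorded before randomisation. Use the approach as intended, never as it stood after conversion, which may occur after allocation.
2. **Decision rule:** declare non-inferiority if the upper limit of the two-sided 95% confidence interval for the adjusted mean difference (no drain minus drain) is below 7.5. The one-sided 2.5% level, the margin and the estimand do not change.
3. **Missing data:** put the same covariates into the imputation model beside treatment group, so that imputation and analysis are consistent.
4. **Sensitivity analysis:** keep the unadjusted one-sided *t* test.

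The cost is a few sentences in the analysis plan, a check that the covariates are on file, and at most three degrees of freedom. No additional patients or visits are needed, and the sample size can stay as it is.

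### Treatment group is the only covariate named for imputing missing CCI, so the imputation as written adds almost nothing to a complete-case analysis and leaves complications already recorded unused

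*Protocol article*

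**What the plan says.** All of this is in the protocol article.

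- **Statistical analysis:** "Missing data for the primary outcome variable will be replaced by using multiple imputation". The method is then described as one "which takes the covariate treatment group into account by application of the fully conditional specification method". Treatment group is the only covariate named. The section mentions no baseline variable, no earlier complication data and no bound on imputed values. The primary analysis is by intention to treat.
- **Outcome parameters:** "The score will be calculated respecting all complications within 3 months after the index operation". On the scale, "A score of 0 indicates no complications, whereas 100 is equivalent to death".
- **Postoperative data collection and blinding:** besides regular ward visits, the schedule in hospital is "Two postoperative study visits (3rd postoperative day and 10th postoperative day/ day of discharge"). Contact later on is by telephone, with "two follow-up telephone interviews after discharge (30 days and 90 days postoperatively").
- **Sample size calculation:** mean CCI 30, SD 20, margin 7.5, 113 analysed per arm; then "With an additional dropout of 10" per cent, 126 are allocated per arm.
- **Minimizing attrition bias:** imputation is presented as the means of limiting bias from incomplete outcome data.

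The article does not say when a CCI counts as missing.

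**The concern.** With one incomplete variable (CCI) and one complete predictor (arm), fully conditional specification has nothing to cycle through. It draws each missing CCI from the fitted distribution in that patient's arm. The imputed arm mean is, in expectation, the observed arm mean, so the analysis reproduces the complete-case difference plus simulation noise. It cannot do the job that the attrition-bias section gives it.

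Useful information is being collected. A patient lost after discharge normally has ward, day-3 and day-10/discharge complications on file, and often day-30 ones. Because the CCI counts every complication up to 90 days, the accrued score is a floor for the final one (assuming that the index never falls when a complication is added). A draw that depends on arm alone ignores that floor.

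At stake is the primary non-inferiority comparison. If patients who drop out of one arm are sicker than those who stay, and the other arm does not show the same pattern, the estimated difference moves although the data that could correct it are on file.

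**Working it through.** **1. The plan's own figures.** With margin 7.5, SD 20, true difference 0, one-sided 2.5% and 80% power, the noncentral t gives 79.8% power at 112 per arm and 80.1% at 113. So 113 is reproduced, and 113/0.90 = 125.6, which rounds up to 126 per arm, 252 in total. The sample size is not in question.

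**2. Draws below the accrued score.** Take a normal draw with the plan's mean 30 and SD 20. The chance of falling below an accrued score c is Φ((c − 30)/20).

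| Accrued CCI | 10 | 20 | 30 | 40 | 45 | 50 |
|---|---|---|---|---|---|---|
| Chance the draw is lower | 16% | 31% | 50% | 69% | 77% | 84% |

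The chance of an impossible value below 0 is Φ(−1.5) = 6.7%. Predictive mean matching on arm alone would keep draws within the scale, but they could still fall below the accrued score.

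**3. Bias in the difference.** Let f be the missing fraction in an arm, and g the mean of the missing patients minus the mean of the observed ones. The true arm mean is observed mean + f·g and the arm-only estimate is the observed mean, so the bias in that arm is −f·g. The bias in the difference (no drain minus drain) is −(f·g in no drain) + (f·g in drain), which is zero when the two products are equal.

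Now assume f·g = 0 in the drain arm. The standard error is 20·√(2/113) = 2.66, and the one-sided error at the margin is Φ(−1.96 + |bias|/2.66).

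| f (assumed) | g (assumed) | Bias | Share of 7.5 | Error at the margin |
|---|---|---|---|---|
| 3% | 10 | −0.30 | 4% | 3.2% |
| 3% | 15 | −0.45 | 6% | 3.7% |
| 10% | 10 | −1.0 | 13% | 5.7% |
| 10% | 15 | −1.5 | 20% | 8.1% |

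If the sicker lost patients are in the drain arm instead, the sign reverses and the test becomes conservative.

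**4. Simulation.** Assumptions: gamma-distributed score with mean 30 and SD 20 (not capped at 100), 80% of it accrued on average before dropout, 126 per arm, 10% missing, true difference 0, 20 imputations, 600 runs. Where dropout depends on the accrued score, the log-odds change by 1 per 20 points.

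| Dropout | Mean difference, arm only | Mean difference, with accrued score | Non-inferiority shown: full data / arm only / with accrued score | Arm-only draws below the accrued score |
|---|---|---|---|---|
| Unrelated to complications | 0.02 | 0.09 | 84% / 80% / 82% | 39% |
| Sicker patients lost, both arms alike | −0.11 | −0.14 | 84% / 86% / 84% | 63% |
| Sicker patients lost, no-drain arm only | −1.82 | 0.04 | 84% / 95% / 84% | 51% |
| Opposite patterns in the two arms | −2.72 | 0.12 | 84% / 98% / 83% | 43% |

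The first two rows show no bias in the difference. In the first, the spread of the estimates is 2.69 with arm only against 2.55 with the accrued score, which is a loss of precision. A plain linear model that includes the accrued score still put about 25% of draws below it, so adding the predictor does not by itself enforce the floor.

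**The case against.** Five points on the other side deserve weight.

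- **The text does not say that treatment group is the sole predictor.** A reader might infer that all others are excluded. The sentence does not say so, a journal article condenses, and an analysis plan that is not shown may list more. This stands, so the finding concerns the wording as published. But that wording is a stated rule with one covariate, and the rule can be judged as written.
- **No missingness rule is given.** If patients lost after discharge are scored on what was seen, draws below the floor never arise for them. This stands too, though that rule would count any unseen later complication as none. The plan has to say which applies.
- **The 10% dropout need not be missing CCI.** The Randomization section removes patients whose distal pancreatectomy is not completed, and they may make up part or all of the 10%. This is why the range above starts at 3%.
- **Direction and size are assumed.** A reader might infer that the imputation favours non-inferiority, or that the true error rate is 6-8%. The article supports neither: it gives no dropout mechanism, and bias needs a difference between arms. Known deaths score 100 and are not missing.
- **Multiple imputation aims at valid arm means, not plausible individual values.** So the 77% figure shows information left unused; it does not measure bias. The simulation also lets dropout depend on the very variable that the remedy adds, so its near-zero residual bias is partly built in.

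**Conclusion.** The point holds in limited form and is worth correcting. As published, the imputation conditions on treatment group and nothing else that is named. It therefore behaves like a complete-case analysis and leaves the recorded complications unused. Whether this distorts the result depends on facts that the article does not give. The difference is biased only if loss to follow-up relates to complications differently by arm, in either direction; otherwise the loss is mainly precision. Under the assumed inputs (3-10% missing in the no-drain arm, those patients 10-15 points worse, no offset in the drain arm) the bias is about −0.3 to −1.5 points, or 4-20% of the margin. This illustrates the possible size and does not predict it.

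**What to change.** Revise the imputation sentence in the Statistical analysis section so that it does four things:

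1. States when a 90-day CCI counts as missing, and in particular how a patient with recorded complications but no day-90 contact is handled.
2. Names the imputation model: treatment group, CCI accrued to last contact (discharge, and day 30 where available) and baseline variables already collected, such as age and ASA class, which eligibility screening requires. Where day-30 scores are themselves incomplete, fully conditional specification then has a real purpose.
3. Bounds imputed values between the accrued CCI and 100. The bound is better built into the draw, for example by predictive mean matching on the increase over the accrued score, than applied by truncating afterwards, because truncation at the floor raises the imputed mean.
4. Adds a delta-shift sensitivity analysis in the no-drain arm, reporting the shift at which the upper confidence limit for the difference reaches 7.5.

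The cost is some wording and a little more analysis code; the sample size does not change. The one requirement on the data is that complications are dated or tied to a visit, so that the accrued score can be calculated. The article does not show whether this is so, and it should be checked before the database is closed.
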